# Population pharmacokinetic modeling of the Qishe pill in three major traditional Chinese medicine-defined constitutional types of healthy Chinese subjects: study protocol for a randomized controlled trial

**DOI:** 10.1186/s13063-015-0568-6

**Published:** 2015-02-26

**Keywords:** Personalized medicine, Individualized medicine, Traditional Chinese Medicine, Multiomics, Population pharmacokinetics

## Abstract

**Background:**

High incidences of neck pain morbidity are challenging in various situations for populations based on their demographic, physiological and pathological characteristics. Chinese proprietary herbal medicines, as Complementary and Alternative Medicine (CAM) products, are usually developed from well-established and long-standing recipes formulated as tablets or capsules. However, good quantification and strict standardization are still needed for implementation of individualized therapies. The Qishe pill was developed and has been used clinically since 2009. The Qishe pill’s personalized medicine should be documented and administered to various patients according to the ancient *TCM* system, a classification of personalized constitution types, established to determine predisposition and prognosis to diseases as well as therapy and life-style administration. Therefore, we describe the population pharmacokinetic profile of the Qishe pill and compare its metabolic rate in the three major constitution types (*Qi-*Deficiency, *Yin*-Deficiency and *Blood-*Stasis) to address major challenges to individualized standardized TCM.

**Methods/Design:**

Healthy subjects (N = 108) selected based on constitutional types will be assessed, and standardized pharmacokinetic protocol will be used for assessing demographic, physiological, and pathological data. Laboratory biomarkers will be evaluated and blood samples collected for pharmacokinetics(PK) analysis and second-generation gene sequencing. In single-dose administrations, subjects in each constitutional type cohort (N = 36) will be randomly divided into three groups to receive different Qishe pill doses (3.75, 7.5 and 15 grams).

Multiomics, including next generation sequencing, metabolomics, and proteomics, will complement the Qishe pill’s multilevel assessment, with cytochrome P450 genes as targets. In a comparison with the general population, a systematic population pharmacokinetic (PopPK) model for the Qishe pill will be established and verified.

**Trial registration:**

This study is registered at ClinicalTrials.gov, NCT02294448.15 November 2014.

**Electronic supplementary material:**

The online version of this article (doi:10.1186/s13063-015-0568-6) contains supplementary material, which is available to authorized users.

## Background

Neck pain is one of the most common symptoms of cervical spine disease. Many treatments are available to patients and considered standard in clinical practice. They include common conservative strategies such as medication, physical methods, manual treatments, and education of patients. However, current evidence for the management of neck pain reveals that conservative interventions, especially Chinese herbal medicine, have not been studied in enough detail to assess their efficacy or effectiveness adequately [1]. Possible reasons for the failure of current clinical practice to effectively manage neck pain lie in two main domains: first, the most difficult challenge faced is clinical heterogeneity, which appears at many levels, such as in the sample group, type of herbal medicine used and outcomes measured [2]; and second, although Chinese proprietary herbal medicines are usually based on well-established and long-standing recipes and formulated as tablets or capsules for commerce, convenience and/or palatability, good quantification and strict detailed standardization still need to be improved.

As individualized diagnostic and therapeutic strategies have become a trend in modern medicine, they might help improve the efficacy and safety, predicting individual outcome and assessing risk, which make individualized prevention and early intervention strategies conceivable and practicable. According to the ancient *TCM* system, a classification of individualized constitution types has been established to determine predisposition and prognosis to diseases as well as therapy and life-style administration [3]. An official Classification and Determination of TCM Constitution [4] was released by the State Administration of TCM and the constitution branch of the Chinese Medical Association in April, 2009. Meanwhile, a standardized scale called Constitution in Chinese Medicine Questionnaire (CCMQ) [5-7] was designed based on the above classification. However, its reliability and validity has not been verified with comprehensive, large sample size trials. In the clinic, it takes a lot of practice for *TCM* specialists to be really efficient at adopting the four *TCM* examinations (observation, listening and smelling, inquiring, feeling the pulse and palpation) to totally assess the participants and determine their constitutional types based on physical, mental, physiological, and pathological attributes, which are called *Ti Zhi.* There are nine kinds of broad constitutional types with a varying degree of predisposition to different diseases (Table 1). Among these, the three most contrasting constitutional types, *Qi-*Deficiency, *Yin*-Deficiency and *Blood-*Stasis, are the most vulnerable to chronic musculoskeletal diseases [3]. In the realm of modern predictive medicine, efforts are being directed toward capturing disease phenotypes with greater precision for successful identification of markers for prospective disease conditions.

**Table 1 Tab1:** **General characteristics of the nine traditional Chinese medicine**
*(*
**TCM) constitutional types** [3,13,14]

	**General characteristics**	**Physical characteristics**	**Psychological characteristics**	**Sign of health**	**Sign of illness**
Gentleness	*Yin-Yang* balanced	Full of vitality and well-proportioned	Mild character	Good cold and hot tolerance, sleep well, good appetite and no fatigue	Less disease
Type A					
*Qi-*deficiency^*^	Insufficiency of primordial *Qi*	Weakened muscle^*^	No desire to speak	Short of breath, listless and low voice and easy to sweat and fatigue	Palpitations and influenza
Type B					
*Yang*-deficiency	More insufficiency of primordial *Qi*	Slightly muscle atrophy	More quiet and introverted	Intolerance of cold, loose stool, clear abundant urine and easy to catch a cold	Diarrhea
Type C					
*Yin*-deficiency^*^	*Yin*-fluid deficiency	Slim body	Quick-tempered	Feverish palms and soles, dry mouth and throat, dry eyes, flushing cheek, and dry skin is usual	Fatigue syndrome, muscle fatigue^*^ and insomnia
Type D					
Phlegm-wetness	Body fluid stasis and phlegm-wetness aggregation	Obese body with accumulate fat around abdomen	Prudent	Feeling body heaviness, chest distress and excessive phlegm, sticky mouth, and sticky sweating in usual	Stroke and Diabetes
Type E					
Wet-heat	Internal accumulation of damp-heat	Slim body	Tend to be irritable	likely to suffer from acne, thirsty, bad breath, bitter taste in the mouth in usual	Constipation, scabies and jaundice
Type F					
Blood-stasis^*^	Poor blood circulation	All body types	Tend to be annoying and forgetful	Frequent pain^*^ and ecchymosis and gloomy complexion	Chronic pain^*^
Type G					
*Qi-*depression	Depression and stagnation of *Qi*	Slim body	Depressive, sensitive and suspicious	Frequently sigh, distention and pain in chest	hypochondria
Type H					
Special diathesis	Special diathesis	All body types	All types	Hypersensitiveness	Asthma and urticaria
Type I					

*The three TCM constitutional types (Qi-deficiency, Yin-deficiency and Blood-stasis) have been selected in this trial.

In the early 1990s, the YQHYTL formula was proposed for neck pain and subsequently underwent further investigation to establish the medicine’s efficacy. Based on the YQHYTL formula, the Qishe pill (Shanghai Sundise Traditional Chinese Medicine Co., Ltd, China), which is composed of processed *Radix Astragali*, *Muscone, Szechuan Lovage Rhizome*, *Radix Stephaniae Tetrandrae*, *Caulis Sinomenii*, and *Calculus Bovis Artifactus* (Table 2), was developed and has been widely used in clinical settings since 2009 [8-11]. The Qishe pill is a thin 0.15 g film-coated pill with a slightly penetrating odor and a mildly bitter flavor. Production and processing of the Qishe pill are described as follows: (1) the volatile oil is extracted from *Szechuan Lovage Rhizome* on standby; (2) the remaining drug decoction from *Szechuan Lovage Rhizome* is mixed with *Radix Astragali,* which has been soaked for 30 min, and simmered in 10 volumes of water, twice, for 2 hours each time; (3) the decoction is then vacuum filtrated to a relative density of 1.24 to 1.26 (70°C), and ethanol is added to the concentrated decoction to bring to a 70% alcohol content; (4) after filtration and concentration (ethanol recovery), the remaining sample is vacuum dried and then crushed into a fine powder; (5) from this mixture, which contains 14 volumes of 70% ethanol, *Radix Stephaniae Tetrandrae* and *Caulis Sinomenii* are extracted with the circumfluent alcohol, three times for 2 hours, concentrated with recovery of ethanol, vacuum dried again, and crushed into a fine powder; (6) the volatile oil of *Szechuan Lovage Rhizome* is then mixed with four parts β-cyclodextrin and dried under vacuum; and (7) the porphyrized powder of the *Calculus Bovis Artifactus* and *Muscone* are mixed with the β-cyclodextrin and the other two fine powders mentioned above, pelleted and coated, to obtain the pills called the Qishe pill (drug name).

**Table 2 Tab2:** **Standard formula (capsule ingredients)***

**Chinese Name**	**Pharmaceutical Name**	**Powered Herb, %**
Huang Qi	*Radix Astragali*	28% (13g)
She Xiang	*Muscone*	0. (0.03g)
Chuan Xiong	*Szechuan Lovage Rhizome*	26% (12g)
Fang Ji	*Radix Stephaniae Tetrandrae*	19% (9g)
Qing Feng Teng	*Caulis Sinomenii*	26% (12g)
Niu Huang	*Calculus Bovis Artifactus*	0. (0.3g)

*Pharmaceutical terminology from Hsu [12].

With the high incidence of neck pain morbidity [13-16], and the wide variety of population properties (age, gender, weight, constitutional type, history of disease and life style, etc.) involved, providing an individual patient with optimal treatment at a given time is challenging. Therefore, personalized administration of the Qishe pill should be documented and practiced with multiple patients. Thus, a comprehensive research concerning the population pharmacokinetics (PopPK) of the Qishe pill in Chinese subjects should be conducted. In this study, we describe the population pharmacokinetic profile of the Qishe pill and compare its extent of metabolism in the three major constitution types (*Qi-*Deficiency, *Yin*-Deficiency and *Blood*-Stasis) to address major challenges of individualized and standardized Traditional Chinese Medicine into clinical practice, as a pilot trial.

## Methods/Design

### Study design

This single-center, three cohort, open-label, double-Latin-sequence, crossover study will be conducted in 108 healthy adult subjects (36 subjects in each cohort) who meet the inclusion and exclusion criteria. The experiments will be conducted in accordance with good clinical practice procedures, all applicable regulatory requirements, and the guiding principles of the Declaration of Helsinki. This study was approved by the ethics committee of the institutional review board in Longhua Hospital, Shanghai University of TCM (2013-LCSY-064). After completing baseline description of the study to the enrolled subjects, written informed consent will be obtained from each of them.

The sample size was established according to GCP guidelines of SFDA, which recommend 8 to 12 subjects in a clinical pharmacokinetic trial. The study will take place at the phase I unit of Longhua Hospital, Shanghai University of TCM from Nov. 2014 to Dec 2016.

### Study population

#### Inclusion and exclusion criteria

We will recruit three main cohorts with confirmed *TCM* constitutional types: *Qi-*Deficiency (n = 36), *Yin*-Deficiency (n = 36) and *Blood-*Stasis (n = 36). All subjects will be 20 to 35 years old and with normal weight (18.5 kg/m^2^ ≤BMI <23.0 kg/m^2^). The detailed inclusion and exclusion criteria are presented in Table 3.

**Table 3 Tab3:** **Inclusion and exclusion criteria**

	**Criteria**
Inclusion	- Aged 20 to 35
	- 18.5 kg/m^2^ ≤body mass index (BMI) <23 kg/m^2^
	- Traditional Chinese medicine (*TCM)-*constitutionally typed as one of the three major types
Exclusion	- History of impaired fasting glucose or diabetes mellitus (past history of diabetes or fasting blood glucose at screening ≥100 mg/dl)
	- History of liver disease (hepatitis, hepatic cirrhosis) or hepatic dysfunction (AST or ALT at screening ≥40 U/L)
	- History of renal dysfunction (creatinine at screening ≥1.2 mg/dl)
	- History of heart disease (heart failure, angina pectoris, myocardial infarction, arrhythmia)
	- History of malignant tumor
	- Having digestive disorders that can interfere with normal absorption of standard diet (gastritis, gastric ulcer, duodenitis, duodenal ulcer, etc.)
	- Smoking during the recent 3 months
	- Alcohol consumption three or more times a week during the recent 3 months
	- Women who were pregnant, intended to become pregnant, or breast- feeding
	- Medicated during the recent month for therapeutic or prophylactic purposes
	- Participating in another clinical trial

All subjects will be surveyed beforehand for their demographic characteristics and lifestyle patterns. The screening will also include blood tests and the Constitution in Chinese Medicine Questionnaire (CCMQ). After exclusion of noneligible participants, the remaining subjects will be assigned identification codes.

### Determination of TCM constitution

According to Classification and Determination of TCM Constitution [4] released by the State Administration of TCM and the constitution branch of the Chinese Medical Association, two TCM specialists will adopt four *TCM* examinations (observation, listening and smelling, inquiring, feeling the pulse and palpation) to totally assess the participants and determine their constitutional types based on physical, mental, physiological, and pathological attributes.

The *TCM* specialists involved are qualified traditional Chinese medical doctors licensed by the Chinese government, with 6 years of traditional Chinese medicine training, minimum 3 years of training in *TCM*, and 9 years of further clinical experience. The constitutional type will be confirmed only when both make concordant decisions. The Constitution in Chinese Medicine Questionnaire (CCMQ) [5-7] will be used to improve objectiveness in decision-making.

### Study procedures

#### Laboratory measurements and clinical assessment

A specific set of laboratory parameters will be measured for every subject on the day of recruitment. These parameters include blood count, electrolyte levels, renal and liver function parameters, blood lipid amounts. Furthermore, age, gender, history of smoking, blood pressure, weight (kg), and height (meters) will be obtained for all subjects. Standard operating procedures have been defined for each clinical examination, including the measurements of blood pressure, height and weight [17].

### Drug administration

Thirty-six healthy adult subjects in each cohort will be randomly divided into three groups to receive three different doses (low, 3.75 g; middle, 7.5 g; or high, 15 g). Subjects will be randomly assigned following simple randomization procedures (computerized random numbers) to each subgroup. Each dose of the Qishe pill (Shanghai Sundise Traditional Chinese Medicine Co., Ltd, China) with the same lot number will be administered orally with water (240 ml) after at least 10-hour fast. The low dose (3.75 mg) was calculated according to the applicable regulatory guidance [18,19], using the No Observable Adverse Effect Level (NOAEL) in the most sensitive species (500 mg/kg/day in Sprague–Dawley rats).

Subjects will be admitted to the study unit the evening before drug administration. On the day of administration, single doses of the Qishe pill will be taken orally, 1h after a standardized meal. Regular standardized meals will be provided 4 h after drug administration. Water is allowed as desired, except for 1 hour before and 2 hours after drug administration. The subjects will remain within a supervised investigational unit for the subsequent 3-d period for pharmacokinetic study and toxicity monitoring, providing 3-day blood and urine samples. Vital signs and clinical laboratory tests were done before and at 24 h after dosing. Furthermore, they will be requested to return to the study unit 4 d after drug administration for a follow-up visit.

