### Sample collection

For the PK analysis and second-generation gene sequencing, 5 ml blood samples will be collected into tubes containing ammonium heparinate and centrifuged immediately at 4000 g for 10 min to obtain plasma samples. These samples will be then transferred into polypropylene vials and kept at −20°C until analysis. For the 7.5 and 15 g dose groups, samples will be collected at dosing (time 0), and 15, 30, 45, 60, 90, 120, 150, 180, 240, 360, 480, 600, 720, 1440, 2160 and 2880 min.

Furthermore, a comprehensive set of biomaterials including EDTA-plasma (6 ml), serum (5 ml) and urine (6 ml) will be collected and stored for future laboratory analyses.

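### Simple randomisation within each cohort of 36 does not fix the dose-group sizes: some group falls below 8 with probability 15% in one cohort and 39% across the nine cohort-by-dose cells

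*Protocol article*

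**What the plan says.** Study design describes a "crossover study will be conducted in 108 healthy adult subjects (36 subjects in each cohort"), so each of the three constitution cohorts has a fixed size. The only basis for the number is this sentence: "The sample size was established according to GCP guidelines of SFDA, which recommend 8 to 12 subjects in a clinical pharmacokinetic trial". No variance, effect size, power or dropout figure accompanies it.

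Under Drug administration, "Thirty-six healthy adult subjects in each cohort will be randomly divided into three groups to receive three different doses" (low, middle and high), and the method follows: "Subjects will be randomly assigned following simple randomization procedures (computerized random numbers) to each subgroup". The abstract agrees on the division: "subjects in each constitutional type cohort (N = 36) will be randomly divided into three groups to receive different Qishe pill doses". Neither place gives a block size, an allocation ratio or a number per dose group.

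**The concern.** An article may leave the details of the randomisation list to the full protocol. Here, however, it names the method, and the method named is unrestricted. Simple randomisation is a sequence of independent draws, so the split of 36 subjects over three doses is random and will rarely be even. If N was built from 12 subjects per cohort-by-dose cell, the stated method does not deliver the layout that the stated N implies.

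Two things are at stake. Cells that turn out small give less precise estimates of any quantity looked at by dose and constitution. The mix of doses will also differ by chance between cohorts, which adds noise to any comparison of exposure between constitutions that does not account for dose. Both are avoidable at no cost in subjects.

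**Working it through.** **Inputs.** From Study design: N = 108, three cohorts of 36, cited range 8 to 12. From Drug administration: three dose groups per cohort, simple randomisation. Assumed, because not stated: allocation 1:1:1 with independent draws (probability 1/3 per dose), and parallel groups, so that each subject counts in one dose group only.

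**Reproducing 108.** 12 × 3 doses × 3 cohorts = 108, which is exact. The lower end of the range gives 8 × 9 = 72. So 108 corresponds to 36/3 = 12 per cell, the top of the cited range.

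**One dose group in one cohort.** The size is binomial(36, 1/3), with mean 12 and SD √(36 × 1/3 × 2/3) = 2.83. P(size < 8) = 0.0514.

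**At least one of three dose groups in one cohort.** By inclusion and exclusion: 3 × 0.05136 − 3 × P(two given groups both < 8). That joint probability is 0.00017, and all three groups below 8 is impossible with 36 subjects. The result is 0.1541 − 0.0005 = 0.1536. Full enumeration of the multinomial gives the same value.

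**At least one of the nine cells.** The cohorts are independent: 1 − (1 − 0.1536)³ = 0.394. A simulation of 400,000 trials gave 0.394.

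**Other features of the same distribution**

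| Quantity | One cohort | Three cohorts |
|---|---|---|
| Exactly 12/12/12 | 2.3% | 0.001% |
| Some dose group < 7 | 6.4% | 18.1% |
| Some dose group < 8 | 15.4% | 39.4% |
| Some dose group < 9 | 31.2% | 67.4% |
| Expected smallest group | 9.1 | 7.8 |

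Within one cohort, the largest and smallest groups differ by 6 or more with probability 49%.

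**Sensitivity.** Sample collection lists sampling times only for two groups ("For the 7.5 and 15 g dose groups, samples will be collected at dosing (time 0")). Counting only those six cells, the per-cohort probability is 2 × 0.05136 − 0.00017 = 0.1026. Over three cohorts it is 1 − (1 − 0.1026)³ = 0.277.

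**What a small cell costs.** At equal SD, the standard error of a cell mean with 8 subjects instead of 12 is larger by √(12/8) = 1.22, or 22%. With 7 subjects it is √(12/7) = 1.31, or 31%.

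**What dose imbalance costs the constitution comparison.** Two cohorts of 36 were compared in an additive model with common variance and dose included. Unequal dose splits inflate the variance of the cohort difference by 3.0% on average (SE about 1.5%), with a 95th percentile of 9%. If dose were ignored, the ratio of the highest to the lowest cohort geometric-mean dose has median 1.17 and exceeds about 1.3 in roughly one trial in ten. That ratio would carry over to exposure only under dose proportionality, which is an assumption.

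**After the change.** Blocks within cohort that close at 12/12/12 put exactly 12 subjects in each cell at randomisation, so P(any cell < 8) = 0 with N = 108.

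**The case against.** Several objections have force.

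- *The floor of 8 is not the plan's own.* The guideline range is quoted for a clinical pharmacokinetic trial. The article does not call 8 a minimum and does not apply it to each cohort-by-dose cell. Pooled over cohorts, the three dose groups average 36 subjects, and the chance that any of them falls below 24 is 1.3%. This stands: 8 per cell is a benchmark suggested by 12 × 9 = 108, not a stated requirement.
- *Simple may be loose wording.* Dividing 36 subjects into three groups could describe a computer-generated split into equal thirds, and the allocation flowchart (Figure 1) is not shown. That is possible. The list would then be sound and the sentence naming the method would need correcting.
- *Crossover.* Study design labels the trial a double-Latin-sequence crossover. If each subject received every dose, numbers per dose would not depend on this randomisation. The abstract, Drug administration and the reference to dose groups in Sample collection all read as parallel groups, and the calculation follows them. The contradiction remains open.
- *Little harm to the main comparison.* Constitution is not randomised, and each cohort stays at 36 whatever the dose split. The population model is parameterised in CL/F and V/F and takes dose as an input. A reader might infer that constitution effects will be confounded with dose. The article plans no unadjusted comparison pooled over dose, and how the noncompartmental AUC and Cmax are compared may be set in an analysis plan that is not shown. That inference is not supported.

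**Conclusion.** The point holds as a modest design weakness. As written, the method does not control the dose-group sizes, and the layout implied by N = 108 is not secured. The chance that some dose group falls below 8 is 15% in a single cohort and 39% for at least one of nine cells. A reader might attach the 39% to one randomisation of 36 subjects, but it belongs to the whole trial.

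The figures rest on parallel groups, independent draws at 1:1:1, and 12 per cell as the intended size. None of the three is settled by the text shown. The consequence is some lost precision in small cells and slight noise from unequal dose mix. Once dose is in the model, the variance cost to the constitution comparison is about 3% on average. Nothing here threatens the validity of the trial. The change is worth making because it costs almost nothing.

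**What to change.** Replace simple randomisation with a concealed, computer-generated permuted-block list at 1:1:1 within each constitution cohort. Block sizes should vary in multiples of three, and each list should close at 12/12/12. State the allocation ratio and the number per dose group in the text. If the existing list is already balanced, correct the description of the method instead.

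Reconcile the parallel-group wording of the abstract and Drug administration with the crossover label in Study design, so that it is clear whether each subject contributes to one dose group or to several.

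The cost is one new list and a few words of text, with N unchanged at 108. The drawback is slight predictability late in a block of an open-label study. Varying block sizes and concealment limit it, and the main outcomes are laboratory-measured concentrations.

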### Pharmacokinetic parameters

The pharmacokinetic parameters of the Qishe pill will be estimated using noncompartmental methods. The actual blood sampling time will be used, and the maximum plasma concentration (*C*_max_) and time to maximum concentration (*T*_max_) will be recorded. The area under the plasma concentration-time curve (*AUC*) will be calculated using the linear trapezoidal rule. The elimination rate constant (*k*_e_ ) will be estimated from the least-squares regression slope of the terminal plasma concentration. The *AUC* from 0 to infinity (*AUC*_0−∞_) will be calculated by (*AUC*_0→t_ + *C*_t_ /*k*_e_ ) (*C*_t_ is the last plasma concentration measured). The elimination half-life (t_1/2_) will be calculated as ln 2/*k*_e_. The distribution volume (DF) will be calculated by Dose/*AUC*/*k*_e_.

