**Figure 3 Fig3:**
[figure not shown]
**Mean plasma concentration-time curves of seven components after oral administration of the Qishe pill at medium and high dosages (n = 4).**

According to the results of the pilot trial, further research should be conducted with modified protocol in dosage setting, requirements of sample collection (diet specifications, blood-collection time window) and sample processing.

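### The dosing instructions set two incompatible prandial conditions for the same single dose, so it is undefined whether the pharmacokinetic parameters are fed or fasted values

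*Protocol article*

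**What the plan says.** Two statements in the Methods/Design section on drug administration fix the state in which subjects take the pill.

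- The first paragraph, directly after describing the three dose levels and the randomisation, says that each dose "will be administered orally with water (240 ml) after at least 10-hour fast".
- The second paragraph, on the procedure in the unit, says that on the day of administration "single doses of the Qishe pill will be taken orally, 1h after a standardized meal".

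Two nearby sentences bear on timing. Before dosing: "Subjects will be admitted to the study unit the evening before drug administration". After dosing: "Regular standardized meals will be provided 4 h after drug administration".

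The results that depend on these doses are set out later. Under Pharmacokinetic parameters, "The pharmacokinetic parameters of the Qishe pill will be estimated using noncompartmental methods"; these include Cmax, Tmax and AUC. Under Medical informatics and data management, the population model is parameterised as CL/F and V/F, with the oral bioavailability F treated as unknown.

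**The concern.** The two sentences describe opposite states for the same act, and that act generates every concentration profile in the study. A meal can change how fast and how completely an oral product is absorbed, so prandial state belongs to the definition of what Cmax, Tmax and AUC measure. The model is exposed in the same way: with F unknown, any effect of a meal on F is carried into apparent clearance and apparent volume.

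The aim stated under Highlights is to find differences in pharmacokinetics between three constitutional types and to base personalised medication on them. If staff followed different sentences for different subjects, unplanned variation in absorption would be added to that comparison. If everyone were handled alike, the comparison within the trial would be protected. A reader of the article still could not say which state the parameters describe, or repeat the study under the same conditions.

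**Working it through.** There is no sample-size, power or alpha figure to reproduce. The check sets the sentences side by side and then looks for any text that would let both stand.

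**Step 1: the two conditions on one time scale.** Put the dose at time 0.

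| Source in Drug administration | Condition | Time since last food at dosing |
|---|---|---|
| First paragraph | fasted | at least 10 h |
| Second paragraph | standardised meal 1 h before the dose | about 1 h |

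Under the second condition the fast falls short of the first by at least 10 − 1 = 9 h. No rounding or time window bridges that gap.

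**Step 2: could the conditions apply to different doses, periods or cohorts?**

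- *Different dose levels.* The fasting sentence covers each dose and follows the list of 3.75, 7.5 and 15 g. The meal sentence refers to the single doses without restriction. Neither is limited to a dose level.
- *Different periods.* Study design states: "This single-center, three cohort, open-label, double-Latin-sequence, crossover study will be conducted in 108 healthy adult subjects". A crossover could in principle have a fed and a fasted period, but none is described in the article.
- *Different cohorts.* The article gives no cohort-specific dosing rule.

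**Step 3: could the fast precede the meal rather than the dose?** The sequence would be an overnight fast, a standardised meal, then the dose an hour later. Evening admission is compatible with this. It is equally compatible with an overnight fast that runs up to the dose. The article does not state the sequence, and the fasting sentence attaches the fast to taking the pill.

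**Step 4: does the later meal settle it?** Food 4 h after the dose fits a fasted dose and a fed dose alike. The limits on water around dosing do not settle it either.

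**Step 5: which results are affected?**

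- Tmax and Cmax depend on the rate of absorption. The sampling schedule given for the 7.5 and 15 g groups places 5 of its 17 times at 0 to 60 min (0, 15, 30, 45 and 60 min), so this phase is closely sampled.
- AUC depends on the extent of absorption. The noncompartmental distribution volume, Dose/AUC/ke, inherits that dependence.
- In the population model, if a meal multiplied F by a factor r and left CL and V unchanged, CL/F and V/F would each be multiplied by 1/r.

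**Step 6: size.** The article gives no human fed-to-fasted ratio, no between-subject variability in humans, and no information on how many subjects would be dosed under each reading. The rat parameters in Table 5 supply none of these. The value of r, the added variability and any bias therefore cannot be computed from the document.

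**The case against.** The best defence is that this is loose wording in a condensed article. On that view the unit intends an overnight fast, a standardised meal and a dose an hour later, and the full protocol says so. That is a coherent reading and may be the true intention. It does not remove the point: the article does not leave the matter open but states two instructions that conflict. If the full protocol is clear, the published text misreports it.

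A second defence concerns the consequences, and most of it stands. This is one centre, one phase I unit, with supervised inpatient stay and standardised meals. The likeliest outcome is that the unit settles on one reading for everyone, which creates no bias between cohorts.

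A reader might infer several stronger claims, and the article does not support them:

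- *That food effects will pass for constitution effects.* This needs fed status to differ systematically by constitutional type, and the article offers no mechanism for that. Any figure for the bias would rest on an assumed food effect combined with an assumed imbalance.
- *That the authors have conceded the present diet rule is faulty.* The Discussion says that after the pilot further research should use a modified protocol, including "requirements of sample collection (diet specifications, blood-collection time window) and sample processing". This lists diet under sample collection and does not say whether the present text already contains the change. It shows that the authors regard diet as relevant, and no more.
- *That a record of meal times or a model term for meal status has been left out.* An article may leave such detail to the full protocol or analysis plan.
- *That subjects have already been dosed under conflicting rules.* Trial status reports recruitment, prescreening and blank control serum, but no dosing. The period November 2014 to December 2016 is given for the study as a whole, not for recruitment.

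**Conclusion.** The plan is wrong as written on this point. The two conditions differ by at least 9 h in time since last food, apply to the same single dose, and are reconciled nowhere in the article. The instruction cannot be followed literally, and the state in which Cmax, Tmax, AUC, CL/F and V/F are measured is undefined. This conclusion rests on the text alone and needs no assumed food effect.

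The consequences are conditional. If practice were mixed, variability in the absorption measures would rise by an amount that cannot be computed here. If practice were uniform, comparisons within the trial would not be harmed by the ambiguity, but the results could not be labelled as fed or fasted. Bias in the constitution comparison is not shown. The point still needs correction before dosing, because prandial state is hard to reconstruct afterwards if it was not recorded.

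**What to change.** Replace the two sentences with a single prandial instruction that applies identically to all 108 subjects, in every cohort and dose group. If a fast before a meal is intended, state the fast, the meal and the dose in order with their intervals. Which condition applies is for the investigators to decide; this review takes no position on it.

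Record the clock time of the last meal before each dose in the case-report form, so that adherence can be checked and the reported parameters can be labelled with the state in which they were obtained. If the full protocol already has one clear rule and records this time, correcting the article is enough.

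The cost is one sentence and one case-report-form field. Sample size, sampling times and analysis method do not change.
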